Does maternal egg consumption lead to improved birth outcomes when compared to birth outcomes of mothers who consume a typical diet (birth outcomes will include miscarriage, stillbirth, preterm births, low-birth weight, small-for-gestational age)?Does any observed effect of maternal egg consumption on birth outcomes (compared to typical diet) differ by child sex (male/female)?Does maternal egg consumption improve other child growth outcomes (including stunting, wasting, and underweight) at 6 months of age compared to a typical diet?Does maternal egg consumption lead to improved levels of micronutrients (iron, vitamin B12, vitamin A) in children at 6 months of age compared to a typical diet?Does maternal egg consumption lead to improved neurodevelopment in utero (as indicated by ultrasound-based measures) or during the first 6 months of life (head circumference, Hammersmith Neonatal Neurological Exam (HNNE), and Caregivers-Reported Early Development Instrument (CREDI) scores compared to typical diet?

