***Secondary outcomes***					
*** Child outcomes***					
* In-utero measurements*	Head circumference z-scores	Continuous (z-score)	INTERGROWTH 21st growth standards	Between 20–26 weeks and 30–34 weeks of gestational ages	Mean (SD)
	Femur length z-scores	Continuous (z-score)	INTERGROWTH 21st growth standards	Between 20–26 weeks and 30–34 weeks of gestational ages	Mean (SD)
	Abdominal circumference z-scores	Continuous (z-score)	INTERGROWTH 21st growth standards	Between 20–26 weeks and 30–34 weeks of gestational ages	Mean (SD)
	Bi-parietal z-scores	Continuous (z-score)	INTERGROWTH 21st growth standards	Between 20–26 weeks and 30–34 weeks of gestational ages	Mean (SD)
	Estimated fetal weight z-scores	Continuous (z-score)	INTERGROWTH 21st growth standards	Between 20–26 weeks and 30–34 weeks of gestational ages	Mean (SD)
	Cerebellar diameter	Continuous (cm)	Ultrasound measurement	Between 20–26 weeks and 30–34 weeks of gestational ages	Mean (SD)
	Corpus callosum length	Continuous (cm)	Ultrasound measurement	Between 20–26 weeks and 30–34 weeks of gestational ages	Mean (SD)
	Thalamus midline axial	Continuous (cm)	Ultrasound measurement	Between 20–26 weeks and 30–34 weeks of gestational ages	Mean (SD)
	Gangliothalamic ovoid diameter	Continuous (cm)	Ultrasound measurement	Between 20–26 weeks and 30–34 weeks of gestational ages	Mean (SD)
	Gangliothalamic ovoid sagittal length	Continuous (cm)	Ultrasound measurement	Between 20–26 weeks and 30–34 weeks of gestational ages	Mean (SD)
	Gangliothalamic ovoid estimated volume	Continuous (cubic cm)	Ultrasound measurement	Between 20–26 weeks and 30–34 weeks of gestational ages	Mean (SD)
* Newborn measurements*	Small for gestational age (SGA) at birth (< 10th percentile and < 3rd percentile)	Binary (two thresholds)	INTERGROWTH 21st growth standards	Within 72 h of birth	Proportion
	Birthweight for gestational age at birth	Continuous (z-score)	INTERGROWTH 21st growth standards	Within 72 h of birth	Mean (SD)
	Preterm live birth (< 37 weeks completed gestation)	Binary	Delivery < 37 + 0 weeks completed gestation	At birth of newborn	Proportion
	Birthweight (g)	Continuous (in g)	Measured using calibrated scale	Within 72 h of birth	Mean (SD)
	Low birthweight	Binary	Birthweight < 2500 g	Within 72 h of birth	Proportion
	Birth weight-for-age z-score	Continuous (z-score)	INTERGROWTH 21st growth standards	Within 72 h of birth	Mean (SD)

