	Small vulnerable newborn status	Binary	Any of: SGA (< 10th), preterm (< 37 weeks), or low birthweight (< 2500 g)	Within 72 h of birth	Proportion
	Head circumference z-score	Continuous (z-score)	INTERGROWTH 21st growth standards	Within 72 h of birth	Mean (SD)
* Infant measurements*	Prevalence of stunting among infants	Binary	Length-for-age < −2 SD according to the WHO Multicenter Growth Reference Study standards	At 6 weeks and 6 months of age	Percentage
	Infant weight-for-age z score	Continuous (z-score)	WHO Child Growth Standards	At 6 weeks and 6 months of age	Mean (SD)
	Prevalence of underweight	Binary	Weight-for-age < -2 SD according to the WHO Multicenter Growth Reference Study standards	At 6 weeks and 6 months of age	Percentage
	Child neurodevelopment- HNNE	Continuous/domain score	Hammersmith Neonatal Neurological Examination (HNNE)	At 6 weeks of age	Domain and total scores
	Child neurodevelopment-CREDI	Continuous	Caregiver-Reported Early Childhood Development Instrument (CREDI) score (long form)	At 6 months of age	Domain-specific scores

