## Statistical methods

### Statistical methods for primary and secondary outcomes {20a}

The primary analysis of the RCT will be based on a modified intention-to-treat (ITT) principle. This trial is designed to formally test the mean difference in the primary outcome of birth LAZ between the treatment arm and the control arm (T1–T2). All women who have a live birth and for whom childbirth length is measured within 72 h will be included in the analysis of the primary outcome. Cases for whom primary outcome data are not available (missing) will not be included in analyses. Descriptive analysis, such as frequency and percentages, will be reported for categorical variables, while means, standard deviation, and quartiles will be reported for continuous variables.

For secondary outcomes, the two-sample *t*-test will be used if the outcome is normally distributed with or without transformation, and the Wilcoxon rank-sum test will be used if the outcome is not normally distributed, where normality will be assessed using the Shapiro–Wilk test and Q-Q plot. Kruskal–Wallis and two-sample rank sum tests will be used if their distribution is non-normal. For both primary and secondary outcomes at birth, exploratory analyses will be conducted using multivariable linear or logistic regression models to adjust for potential confounders (such as baseline SES, gestational age at birth, mother’s education, mother’s age, and dietary diversity) that may be imbalanced across treatment arms. Imbalance of baseline factors may occur as a post-randomization selection bias or by chance alone. Post-randomization selection bias is possible, especially given that participants are not blinded. If this occurs, it will be crucial to adjust for imbalanced confounders in all regression analyses. Village-level heterogeneity will be considered using random effects. Spatial correlation in village-level random effects will be adjusted for if spatial clustering patterns in the outcomes are present. For longitudinal outcomes such as head circumference, linear or generalized linear mixed models will be used to account for heterogeneity in the intercept and slope of growth.

All statistical analyses will be conducted using R and Stata. The statistical significance for regression models will be set at *p* < 0.05 without further adjustment for multiple comparisons.

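### Gestational age at birth is listed as a confounder in the exploratory adjusted models, although it is fixed after randomisation and is itself a trial outcome; with it, the preterm-birth model cannot be estimated

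*Protocol article*

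**What the plan says.** Section {20a} of the protocol article sets the formal comparison as the difference in mean birth LAZ between arms. Secondary outcomes get a t-test or a rank test. It then adds a layer of adjusted models: "For both primary and secondary outcomes at birth, exploratory analyses will be conducted using multivariable linear or logistic regression models". Their purpose is "to adjust for potential confounders (such as baseline SES, gestational age at birth", with the mother's education and age and dietary diversity also named), described as factors that may differ between arms. After a remark on post-randomisation selection bias, it says that if such bias occurs "it will be crucial to adjust for imbalanced confounders in all regression analyses".

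Elsewhere the same quantity is an outcome. Table 1 has preterm live birth as a secondary newborn outcome, defined as "Delivery < 37 + 0 weeks completed gestation". The small vulnerable newborn composite contains it: "Any of: SGA (< 10th), preterm (< 37 weeks), or low birthweight (< 2500 g". Section {7} asks whether eggs improve birth outcomes and specifies that "birth outcomes will include miscarriage, stillbirth, preterm births, low-birth weight, small-for-gestational age".

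**The concern.** A covariate used to remove confounding in a randomised trial must be settled before assignment. Gestational age at birth is settled at the end of the intervention, and the trial hypothesises that the intervention may change it. The plan thus treats length of gestation both as something eggs may alter and as a nuisance to be held constant.

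Three things are at stake:

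- **Preterm birth.** The outcome is a cut-off on the covariate, so the model has no finite solution.
- **Outcomes not standardised for gestation.** The adjusted estimate answers a different question, namely the effect other than through gestation, while being presented as the confounder-adjusted effect.
- **All outcomes at birth.** If unmeasured factors influence both gestation and fetal size, conditioning on gestation can bias the comparison (collider bias).

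Binary outcomes at birth are the most exposed. The t-test, Wilcoxon and Kruskal–Wallis tests in {20a} are not methods for yes/no outcomes, and its mixed models are for longitudinal data. That leaves this logistic regression as the only inferential method the section names for preterm birth, low birthweight, SGA and small vulnerable newborn.

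**Working it through.** **1. Timing.** Eggs are given from first-trimester enrolment to childbirth (section {6b}). Gestational age at birth becomes known at delivery, so it follows assignment. Section {7} and Table 1 make preterm birth an outcome, so a path from eggs through gestation to birth size is part of the trial's own hypothesis.

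**2. The plan's own figure.** Section {14} gives a difference of 0.18 LAZ, one-sided 5% level, 80% power and 20% attrition. The SD is not stated; 1 is assumed.

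- n = 2 × ((1.6449 + 0.8416) / 0.18)² ≈ 381.6, so 382 per arm
- 382 / 0.80 = 477.5, so 478 per arm, as stated

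No covariate enters this calculation, so the point does not touch it. The simulations below use 382 analysed births per arm.

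**3. Preterm birth.** Preterm = 1 exactly when gestational age at birth is below 37 weeks, so the covariate separates the outcome completely. In one simulated data set (6.8% preterm), the longest preterm gestation was 36.98 weeks and the shortest term gestation 37.01. The logistic fit did not converge. The gestational-age coefficient ran from −14 to −78, −359 and −1202 as iterations increased, and the standard error of the arm effect rose from 0.7 into the thousands.

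**4. Birthweight in grams.** Let eggs shift gestation by δ weeks, birthweight rise β g per week, and the direct effect be τ. The total effect is τ + βδ. With gestational age at birth in the model, the arm coefficient estimates τ, so βδ is lost. The documents give neither β nor δ; all values here are assumptions.

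- δ = 0: loss 0 g, whatever β
- δ = 2/7 week: 2/7 × 100 = 29 g; 2/7 × 200 = 57 g
- δ = 0.1 to 0.3 week at 150 g per week: 15 to 45 g

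Simulated means over 400 runs, at 150 g per week:

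| Shift in gestation (weeks) | Direct effect (g) | Without gestational age at birth (g) | With it (g) |
|---|---|---|---|
| 0.1 | 0 | 17 | 1 |
| 0.2 | 0 | 29 | −1 |
| 0.3 | 0 | 43 | −1 |
| 0.1 | 50 | 64 | 50 |
| 0.2 | 50 | 78 | 50 |
| 0.3 | 50 | 93 | 49 |

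**5. LAZ and other gestation-standardised scores.** The same formula applies with β as the residual slope of the z-score on gestational age. With no residual slope, the simulated effect is 0.18 with or without adjustment. With slopes of 0.05 and 0.10 per week and δ = 0.2, the shift is 0.05 × 0.2 = 0.01 and 0.10 × 0.2 = 0.02. A larger shift needs an unmeasured common cause. With δ = 0.3 week and such a cause assumed to act on both gestation and LAZ, the estimate fell from about 0.18 to 0.16 or 0.13, depending on the strength of that cause.

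**6. Selection by imbalance.** If a factor were flagged at p < 0.05 (an assumption; {20a} sets no criterion), the chance of flagging at least one of five independent baseline factors would be 1 − 0.95⁵ = 22.6%. With gestational age at birth on the list, a real effect of eggs on gestation would also look like an imbalance and call for its own removal.

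**The case against.** The strongest defence is that these models are labelled exploratory. The formal test is the LAZ comparison, and continuous secondary outcomes such as birthweight get an unadjusted t-test or Wilcoxon test, so their total effects are still reported. The list opens with wording that makes it illustrative, and an analysis plan that is not shown may set the covariates outcome by outcome. This limits the severity. It does not remove the point, because the variable is named, no outcome at birth is exempted, and binary outcomes have no other named inferential method.

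Some stronger readings go further than the document allows:

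- *The primary result is compromised, or LAZ is harmfully adjusted twice.* The primary comparison is separate, and adjusting an already standardised score changes it by 0 to 0.02 in the cases tried. Only the collider scenario moves it more, and that rests on assumed inputs.
- *Several birth outcomes become inestimable.* Only preterm birth is an exact function of gestational age. Term babies can be small or of low birthweight, so the composite and low birthweight can still be fitted.
- *Covariates are chosen by a data-driven rule.* The text is loose. It names factors in advance, sets no threshold, and ties its strongest sentence to selection bias having occurred. Imbalance-driven selection is a fair reading but not the only one.
- *Dietary diversity means a follow-up value.* It carries no baseline label and is also a repeated outcome in Table 1. However, {20a} goes on to speak of baseline factors and the enrolment data collection in section {18a} includes it, so the enrolment value is the natural reading.

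**Conclusion.** The point holds for gestational age at birth and should be fixed. Listing it as a confounder contradicts the trial's own use of preterm birth as an outcome of eggs. That the preterm logistic model cannot be estimated with this covariate follows from the definitions and needs no assumption. The loss for outcomes not standardised for gestation depends on eggs changing gestation: none if they do not, and about 29 to 57 g of birthweight for a 2-day lengthening at 100 to 200 g per week. Low birthweight and small vulnerable newborn are affected in the same direction; no size was worked out for them. For LAZ and the other standardised scores the effect is small apart from possible collider bias. The unadjusted primary comparison and the 478 per arm stand.

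**What to change.** In section {20a}:

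- Delete gestational age at birth from the covariate list.
- State that dietary diversity means the value at enrolment.
- Adjust only for prespecified variables measured before randomisation: the listed baseline factors (SES, mother's education, mother's age, enrolment dietary diversity) plus the gestational-age stratum used in the randomisation. Drop the wording that ties adjustment to observed imbalance.

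This is a change of wording. It needs no new data and leaves the sample size as it is. Enrolment is reported as paused (Trial status), so the change can be made before analysis.

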### Methods for additional analyses (e.g., subgroup analyses) {20b}

Subgroup analyses will be performed to assess effect modification of any treatment effect by dietary diversity, compliance with study supplement use, coexisting medical conditions, BMI, and infant gender on our study results, with proper attention to the effects of multiple comparisons on the ability to draw conclusions.

### Methods in analysis to handle protocol nonadherence and any statistical methods to handle missing data {20c}

Per-protocol analysis will be performed as a sensitivity analysis. Per-protocol is defined as completing 80% of the scheduled daily doses in the treatment arm from enrollment until birth. Additionally, we may include actual doses or dose groups instead of the assigned treatment arms in the regression models. Missing data will be treated as missing for the primary outcome.

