### Intervention description {11a}

All women enrolled in the study will be asked to visit a designated village-based consumption site (CHW’s home) daily. Sites must be within a 20-min walk from women’s homes. When a CHW house is not within a 20-min walk, additional sites (such as the home of a World Vision volunteer) will be identified close to the participant’s house. Study staff will prepare and transport hard-boiled eggs daily to CHWs’ houses (or designated consumption site), where CHWs will distribute eggs to the women in the intervention group every day. Study staff will observe and record consumption (no consumption, partial, or complete). The study staff will also ask about 24-h recall of quantity and consistency of CSB+ consumption and any adverse reaction or allergy to eating eggs. Women in the treatment arm and the control arm will both receive IEC communication. All women (treatment and control) will be compensated for their daily travel to the CHW’s house. The daily compensation of 500 RWF per day will be paid on a weekly basis if women attend at least 6 days in a week. However, in cases of excused absence, they will receive daily compensation for those days.

Participants in both the intervention and control groups will receive guidance to maintain their usual diets outside of the study intervention. No dietary restrictions will be imposed.

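### The 80% per-protocol rule binds the egg arm only, and compliance and dose enter as post-randomisation factors, so these secondary analyses are biased whenever adherence is related to prognosis

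*Protocol article*

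**What the plan says.** The section on nonadherence and missing data {20c} gives the role of the analysis, "Per-protocol analysis will be performed as a sensitivity analysis", and then its population: "Per-protocol is defined as completing 80% of the scheduled daily doses in the treatment arm from enrollment until birth". No condition is set for women in the control arm. The same section adds an option: "we may include actual doses or dose groups instead of the assigned treatment arms in the regression models".

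The section on additional analyses {20b} plans subgroup analyses of "effect modification of any treatment effect by dietary diversity, compliance with study supplement use, coexisting medical conditions, BMI, and infant gender".

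Three other places bear on the point:

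- Section {20a} sets the main analysis: "The primary analysis of the RCT will be based on a modified intention-to-treat (ITT) principle". It uses live births with length measured within 72 h and does not refer to adherence.
- Section {11a} asks daily attendance of both arms: "All women enrolled in the study will be asked to visit a designated village-based consumption site (CHW’s home) daily".
- Sections {11b} and {11c} give the reasons why egg consumption may stop or be missed. These include severe illness, adverse events, withdrawal, sickness, travel, and work or family commitments.

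**The concern.** Randomisation makes the arms comparable as assigned. The 80% rule removes the low adherers from the egg arm, while the control women who would have behaved in the same way stay in. If low adherers differ in prognosis, part of the per-protocol difference reflects who was removed and not what eggs do.

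The other two analyses share the root problem. Compliance is observed after assignment. If it means egg compliance, it has no counterpart among controls, so a treatment-by-compliance interaction has no comparison group. A model with dose in place of arm uses an exposure that the women themselves determine, and so gives up the protection of randomisation.

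At stake is how the main result will be read. The per-protocol analysis is the only one that the article calls a sensitivity analysis. If it differs from the primary result, the reader cannot tell an effect of fuller adherence from selection.

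**Working it through.** **The plan's own figure.** Section {14} gives a difference of 0.18 LAZ, one-sided 5%, 80% power and 20% attrition. No SD is stated; SD = 1 is assumed because the outcome is a z-score.

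- n per arm = 2 × (1.645 + 0.842)² / 0.18² = 382 after rounding up.
- 382 / 0.8 = 478 after rounding up, as stated. The sample size is not in dispute, and 382 evaluable women per arm is used below.

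**Selection model.** Suppose eggs have no effect. Let q be the share of the egg arm that fails the 80% rule, and ρ the correlation between the tendency to adhere and LAZ, both normal. Neither q nor ρ is in the documents. All controls are kept. With z the q-quantile of the standard normal and φ its density:

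- m = φ(z) / (1 − q)
- spurious difference = ρ × m
- variance in the retained egg arm = 1 − ρ² × m × (m − z)
- SE = √[variance / (382 × (1 − q)) + 1/382]
- one-sided rejection rate = 1 − Φ(1.645 − difference/SE)

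**One cell in full (q = 20%, ρ = 0.2).** z = −0.842 and φ(z) = 0.280, so m = 0.280/0.8 = 0.350. The difference is 0.2 × 0.350 = 0.070, which is 39% of 0.18. The variance is 1 − 0.04 × 0.350 × 1.192 = 0.983. SE = √(0.983/305.6 + 1/382) = 0.076. The rejection rate is 23% where 5% is intended.

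**Grid: spurious LAZ difference (one-sided type I error)**

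| Excluded from egg arm | ρ = 0.05 | ρ = 0.1 | ρ = 0.2 | ρ = 0.3 |
|---|---|---|---|---|
| 10% | 0.010 (6.5%) | 0.019 (8.3%) | 0.039 (13.2%) | 0.058 (19.7%) |
| 20% | 0.017 (7.8%) | 0.035 (11.7%) | 0.070 (23.3%) | 0.105 (39.6%) |
| 30% | 0.025 (9.1%) | 0.050 (15.4%) | 0.099 (34.8%) | 0.149 (59.8%) |
| 40% | 0.032 (10.4%) | 0.064 (19.1%) | 0.129 (46.3%) | 0.193 (76.0%) |

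Tested two-sided, the rejection rate runs from 5.2% to 65.2% over the same grid. At ρ = 0 the difference is zero in every row. A negative ρ gives the same sizes with the sign reversed. If one criterion were applied to both arms and adherence behaved alike in both, the expected difference under no effect would be about zero.

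**Compliance and dose.** Here the check is of the text. Section {20b} speaks of the study supplement. Section {11c} uses that word for the eggs, but the abstract also calls the flour given to both arms a supplement. If eggs are meant, controls have no value. If flour is meant, both arms have a value, but it is still measured after assignment. For dose, section {20c} states that it would stand in place of the arm, not beside it.

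**The case against.** The strongest reply is that nothing central depends on these analyses. The primary comparison ignores adherence, per-protocol is a sensitivity analysis, the dose model is optional, and section {20b} promises care over multiple comparisons. This stands and limits the point to secondary analyses, although care over multiplicity does not remove selection.

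A reader might go further in four ways that the documents do not support.

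- **That the bias favours eggs.** Sickness as a reason for missed doses points that way. But attendance earns 500 RWF a day, so poorer women may attend more and employed women less, which could reverse the sign.
- **That the bias is large.** That needs a high correlation and many exclusions. Telephone follow-up, same-day home visits and delivery of eggs in hospital (section {11c}) aim at full adherence, so the 10% row is as plausible as the others. Section {20a} also plans exploratory adjustment for baseline SES, education, age and dietary diversity, which would remove some selection but not the unmeasured part.
- **That a dose analysis restates gestational length.** A raw count does rise with later birth: 4 weeks × 7 days × 2 eggs = 56. But section {20c} does not specify a cumulative count, and the only adherence measure it defines is a proportion of scheduled doses. Section {20a} lists gestational age at birth as a possible covariate, and the primary outcome is an age-standardised z-score.
- **That effect modification by compliance can never be estimated.** This holds only if compliance means eggs, which the text leaves ambiguous.

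The remedies have limits too. With no study eggs in the control arm, the complier estimate is essentially the ITT difference divided by mean adherence, so it adds little evidence on whether an effect exists. An equal attendance rule need not select comparable women, because incentives differ by arm and egg-arm women who miss the site may receive eggs at home.

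**Conclusion.** The point holds for the secondary analyses and should be corrected. As written, the per-protocol contrast sets selected egg-arm women against all controls, compliance is a post-randomisation subgroup factor, and a self-selected dose may replace the randomised arm. Each is biased whenever adherence is related to prognosis, which the stated reasons for missing or stopping eggs make plausible but do not prove.

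With no true effect, the illustrated per-protocol bias runs from 0.01 LAZ (5% of the 0.18 design effect) to 0.19 LAZ (107%), and is zero at zero correlation. The range rests on assumed exclusion shares of 10% to 40%, assumed correlations of 0.05 to 0.3, SD 1, a normal selection model and no covariate adjustment. The documents fix neither its size nor its sign. A reader might infer that the trial's main result is compromised. It is not, because the modified-ITT comparison does not use adherence.

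**What to change.** 1. **Replace the one-arm per-protocol analysis** in section {20c} with a complier average causal effect. Use randomised arm as the instrument and the proportion of scheduled egg-days consumed as the exposure. State that section {11d} leaves control egg intake unrestricted, so the estimate concerns the supervised eggs on top of usual intake.
2. **If a per-protocol set is kept**, apply the same recorded daily-attendance criterion to both arms and adjust for baseline covariates. Do not use the payment record, because excused absences are also paid. State that comparability of the two sets is not guaranteed.
3. **Delete compliance** from the subgroup list in section {20b}.
4. **Label any dose model as observational**, with the proportion of scheduled days as the exposure.

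The cost is analysis wording and a wider confidence interval for the complier estimate. Egg consumption is already recorded daily. Payment depends on attendance in both arms, so attendance should be known for controls, but the team should confirm that it is stored separately from payment. The trial status section reports that enrolment is paused, so the wording can be settled before it resumes.
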